## Assignment of interventions: Blinding

### Who will be blinded {17a}

Not applicable; this is an open-label study.

### Procedure for unblinding if needed {17b}

Not applicable; this is an open-label study.

## Data collection and management

### Plans for assessment and collection of outcomes {18a}

The primary outcome will be assessed on every study visit and extra visits. For detailed information about data collected on each visit, see Table 2 (SOA). Data are reported in the eCRF. PROMs will be collected directly in the eCRF using tablets. All study personnel will undergo training before trial initiation and repeated annually during data collection.

### Plans to promote participant retention and complete follow-up {18b}

Given the eligibility criteria, all participants in this study have been under long-term follow-up from before study start and thus have an established relationship with the clinic. Participants will be given a direct number to the study nurse or clinic for contact regarding the study, the medications, side effects, or if they suspect a disease flare. If a participant chooses to leave the study, he or she will be scheduled for an early discontinuation visit and thereafter be followed in clinical practice.

### Data management {19}

Data are reported directly in the eCRF, Viedoc, which requires two-factor authentication. The investigator must permit study-related monitoring, audits, ethics committee review, and regulatory agency inspections and provide direct access to source documents. Records and documents, including signed informed consent forms, must be retained by the investigator for 25 years after study completion unless local regulations or institutional policies require a longer retention period. No records may be destroyed during the retention period without the written approval of the sponsor. No records may be transferred to another location or party without written notification to the sponsor. Independent data monitoring is organized by the Clinical Trial Unit, Oslo University Hospital.

### Confidentiality {27}

Informed consent signed by both the participants’ legal guardians is required prior to any data collection in the eCRF. Patient confidentiality will be maintained according to the data privacy statement in the informed consent form.

### Plans for collection, laboratory evaluation, and storage of biological specimens for genetic or molecular analysis in this trial/future use {33}

Routine laboratory tests will be analyzed locally at each participating site. Assessment of drug and anti-drug antibody levels will be analyzed at the Department of Biochemistry at Oslo University Hospital, Radiumhospitalet, Norway. Biobanking of blood will be collected at every visit. Biobank samples will be stored locally in a freezer at − 70 to − 80 °C until all biobank material is collected. At the end of the study, biobank material will be shipped to the sponsor according to procedure.

## Statistical methods

### Statistical methods for primary and secondary outcomes {20a}

The sample size was determined by using R-function *ssc_propcomp* (non-inferiority hypothesis) in *SampleSize4ClinicalTrials* -package (R Foundation for Statistical Computin, Vienna, Austria). R or statistical software for data science (STATA) will be used to analyze the results of the study.

The main analyses will be performed according to a predefined Statistical Analysis Plan (SAP) when all participants have concluded the study, all data have been entered, verified, and validated, and the database has been locked. The SAP can be provided upon request to the authors. The intention-to-treat (ITT) set will include all patients randomly assigned to a treatment group irrespective of post-randomization occurrences. The per-protocol analysis set (PPS) will include all randomized patients meeting the study entry criteria who followed the study protocol with no major protocol deviations. The primary analyses will be performed based on the PPS. Due to the non-inferiority setting, a per-protocol approach was chosen to assess the effect among participants who adhered to the protocol to avoid bias toward no treatment difference, thereby reflecting the effect under optimal implementation, while the ITT set will be used for sensitivity analysis. The safety analyses will be performed using the ITT set.

Baseline characteristics will be summarized descriptively by treatment group using mean and standard deviation or median and interquartile range for continuous variables, and counts and percentages for categorical variables.

The primary objective of the trial is to assess the non-inferiority of each of the drug withdrawal groups B and C to control group A. The two primary hypotheses are the following:Group B (withdrawal of MTX, stable TNFi) is non-inferior to group A (stable MTX and TNFi), i.e., the difference between the groups in the proportions of study participants having disease flares during the 12-month follow-up period is less than or equal to the pre-specified non-inferiority margin of 20%.Group C (withdrawal of TNFi, stable MTX) is non-inferior to group A (stable MTX and TNFi).

As two primary non-inferiority tests are performed simultaneously, a Bonferroni correction will be applied, and primary endpoints tested at the 0.025 level to control the overall probability of Type I error. The non-inferiority of groups B and C to group A will be evaluated by estimating a risk difference and its 97.5% confidence interval from the logistic regression model with disease flare as a binary outcome and treatment group and stratification variables (study site and JIA course (persistent oligoarticular JIA versus other non-systemic JIA categories)) as covariates. The upper bound of this confidence interval will be compared to the non-inferiority margin of 20%. Non-inferiority is claimed if the primary null hypothesis is rejected at the significance level of 0.0125 (one-sided), that is, if the upper limit of the 97.5% two-sided confidence interval for the treatment difference is less than 20%. In case the primary null hypothesis (1) or (2) is not rejected (group B/C is inferior to group A), the superiority of group A to group B/C will be examined (key secondary).

Key secondary objective is to compare the disease flare rates during the first 12 months follow-up in two drug withdrawal groups B and C. The key secondary hypothesis is that the risk of disease flare during the first 12 months of follow-up is equal in arm B (withdrawal of MTX with stable TNFi) and arm C (withdrawal of TNFi with stable MTX). The comparison will be performed as a two-sided superiority test by estimating a risk difference and corresponding 95% confidence interval from the logistic regression model with disease flare as a binary outcome and treatment group and stratification variables (study site and JIA course (persistent oligoarticular JIA versus other non-systemic JIA categories)) as covariates. Based on the results, the direction and the clinical relevance of the difference may be examined.

The results of the trial will be reported according to consolidated standards of reporting trials (CONSORT).

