### Sample size {14}

The primary objective is to assess the non-inferiority of each of the drug withdrawal groups B and C to control group A in terms of disease flare (yes/no) during the 12-month follow-up. Due to two primary comparisons, a Bonferroni correction is applied to account for multiple testing, resulting in a significance level of 2.5%. Further, non-inferiority is assessed by comparing the upper bound of the 97.5% confidence interval of the risk difference to the pre-specified 20% non-inferiority margin. Thus, a significance level of 1.25% is used when determining the required sample size.

Available data suggest that the rate of disease flare when continuing stable treatment (group A) is approximately 10%. Due to the non-inferiority set-up, we assume that the risk of disease flare is equal in all three groups. Using a non-inferiority margin of 20%, power of 80%, and significance level of 1.25%, we estimate that randomization of 43 patients per group would be required. Assuming a 15% drop-out rate, a total of 150 participants will be randomized.

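### Non-inferiority can be claimed on the per-protocol set alone, with no rule for when the ITT analysis disagrees

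*Protocol article*

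**What the plan says.** All references are to the protocol article. Under Statistical methods for primary and secondary outcomes {20a}, "The primary analyses will be performed based on the PPS". That set holds "all randomized patients meeting the study entry criteria who followed the study protocol with no major protocol deviations". The reason given is that "a per-protocol approach was chosen to assess the effect among participants who adhered to the protocol to avoid bias toward no treatment difference", "while the ITT set will be used for sensitivity analysis". The same section claims non-inferiority at one-sided 0.0125 for each comparison, that is, "if the upper limit of the 97.5% two-sided confidence interval for the treatment difference is less than 20" per cent. The claim rule does not mention the ITT result.

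Other sections bear on the point:
- Intervention description {11a}: participants and clinicians know the allocation; the statistician for the primary outcome is blinded.
- Outcomes {12}: a flare is either a JADAS-27 rise with an active joint, or agreement between physician and family on a clinically significant flare that needs more DMARD treatment.
- Criteria for discontinuing or modifying allocated interventions {11b}: in groups B and C, baseline drugs are restarted after a flare; pauses for infection or adverse events are allowed.
- The missing-data section {20c}: a missing primary outcome is counted as a flare.

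**The concern.** The per-protocol set conditions on what happens after randomisation. It guards against dilution of a true difference only if deviating is unrelated to the risk of flare. In this trial families and clinicians know who is tapering. Groups B and C have a taper that can be abandoned, and group A has none. If a child with early symptoms goes back on the drug outside the protocol, and this is classed as a major deviation, a likely flare leaves the withdrawal arm. That moves the estimate toward non-inferiority.

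Counting missing outcomes as flares does not repair this, because a patient excluded from the primary set is no longer there to be imputed. The headline claim could then rest on a non-randomised comparison that the ITT analysis contradicts, and the plan has no rule that lets the ITT result count.

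**Working it through.** **Inputs.** From Sample size {14}: control flare rate 10%, equal rates assumed, margin 20 points, one-sided 1.25%, power 80%, 43 per group, 150 randomised (50 per group) with 15% drop-out. The article gives no rate or pattern of per-protocol exclusions, so those below are assumptions.

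**Step 1: the plan's own figure.** n = [p(1−p) + p(1−p)] × (z₀.₉₈₇₅ + z₀.₈₀)² / margin² = 0.18 × (2.241 + 0.842)² / 0.04 = 42.8, so 43 per group. This reproduces.

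**Step 2: how few exclusions reverse the result.** Upper limit = RD + 2.241 × √[p₁(1−p₁)/n₁ + p₂(1−p₂)/n₂].
- ITT, 5/50 against 10/50: RD = 0.100, SE = 0.0707, upper limit = 0.100 + 2.241 × 0.0707 = 25.8%. Non-inferiority is not shown.
- Remove three would-be flares from the withdrawal arm, 5/50 against 7/47: RD = 0.0489, SE = 0.0671, upper limit = 0.0489 + 2.241 × 0.0671 = 19.9%. Non-inferiority is claimed.

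**Step 3: false-claim rate at the margin.** True rates are 10% in A and 30% in a withdrawal arm, with 43 per arm before exclusions. The rate is the exact binomial probability that the Step 2 limit falls below 20%. If a fraction f of would-be flares leaves the withdrawal arm, its rate becomes 0.30(1−f) / [0.30(1−f) + 0.70].

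| Exclusions | Withdrawal arm as analysed | False-claim rate |
|---|---|---|
| None | 30%, n = 43 | 1.6% |
| f = 1/5 | 0.24/0.94 = 25.5%, n = 40 | 5.5% |
| f = 1/3 | 0.20/0.90 = 22.2%, n = 39 | 12.2% |
| f = 1/5, plus 10% of that arm's non-flaring patients | 0.24/0.87 = 27.6%, n = 37 | 3.4% |
| f = 1/3, plus 10% of that arm's non-flaring patients | 0.20/0.83 = 24.1%, n = 36 | 8.1% |
| f = 1/5, same fraction of A's flares also leaving | 25.5%, n = 40 | 4.1% |
| f = 1/3, same fraction of A's flares also leaving | 22.2%, n = 39 | 7.2% |

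The nominal level is 1.25%; 1.6% is what this interval gives with no exclusions.

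**Step 4: requiring both sets.** A joint rule cannot claim more often than ITT alone. With ITT outcomes observed, that is 1.6% whatever leaves the per-protocol set.

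Power was simulated at 10% against 10%, 50 per arm, with 15% leaving the per-protocol set for reasons unrelated to outcome:
- Per-protocol set alone: 79.8%.
- Both sets, ITT outcomes observed: 78.1%.
- Both sets, that 15% missing and counted as flares in ITT: 52%. Each arm's ITT flare rate becomes 0.10 + 0.90 × 0.15 = 23.5%, and ITT power alone is about 55%.

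The calculations use an unadjusted Wald interval, not the covariate-adjusted risk difference from the logistic model, so they are approximate.

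**The case against.** The strongest objection is that the endpoint absorbs much of the mechanism. The consensus limb of the flare definition needs neither a JADAS change nor an active joint. A restart that physician and family agree is for a clinically significant flare therefore counts as an event, and the return to baseline treatment is then directed by the protocol. An extra visit within two weeks of a suspected flare (Participant timeline {13}) makes that route more likely. This stands. A reader might infer that every symptom-driven restart removes a flare from the analysis; the article does not support that. What remains is narrower: families who resume on their own, and restarts that the physician does not call a flare.

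It is also fair that only major deviations exclude a patient, that their definition may sit in the unseen SAP, and that the exclusion fractions above are assumptions loaded on one arm. The lower rows of the table show how far the inflation shrinks otherwise. The blinded statistician helps, but the deviations arise among people who are not blinded. The dilution argument for a per-protocol analysis is a recognised one; it supports having that analysis, not letting it decide alone.

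A reader might also infer that the stated 80% power is wrong because the sample size allows only for drop-out. That does not follow. With 150 × 0.85 / 3 = 42.5 per arm, power is 79.7%, which is rounding, and any further loss is undocumented. The article also does not say whether drop-outs stay in the per-protocol set with an imputed flare.

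**Conclusion.** The point holds in a limited form. As written, a per-protocol pass is a claim of non-inferiority even if ITT fails, and the rationale addresses only one direction of bias. Three outcome-related exclusions from one arm of 50 can reverse the conclusion. Losing one fifth to one third of would-be flares from one withdrawal arm raises the false-claim rate from 1.6% to about 5.5–12%, or about 3.4–8.1% if that arm also loses 10% of its non-flaring patients. The size rests wholly on assumed exclusions. The absence of a rule for disagreement does not; it is in the text. The SAP may define major deviations, but a requirement that the sets agree would change the decision rule that this article states.

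**What to change.** Claim non-inferiority only if the upper 97.5% limit is below 20% in both the ITT set and the per-protocol set. Fix per-protocol membership before the analysis, by people blind to arm and outcome.

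Two things must go with this:
- Keep recording flare to month 12 in patients who deviate or stop allocated treatment, so that ITT outcomes are observed.
- State how the impute-as-flare rule applies to the ITT set. One option is multiple imputation for the agreement test, with impute-as-flare as a sensitivity analysis.

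The cost is an amendment to protocol and SAP wording, plus continued follow-up of deviators. Joint power is about 78% against about 80% for the per-protocol set alone if ITT outcomes are largely observed. It drops to about 52% if 15% are missing and counted as flares, so the joint rule should not be adopted without settling imputation. Trial status reports 40 participants included of the 150 planned, so the change can be made well before any outcome analysis.

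### A Holm step-down in place of single-step Bonferroni would raise power for the two primary non-inferiority claims at the same familywise error; the current rule is valid, so this is an inexpensive improvement and not a correction

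*Protocol article*

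**What the plan says.** Under Statistical methods for primary and secondary outcomes {20a}, the protocol article names two primary hypotheses of equal rank: B is non-inferior to A, and C is non-inferior to A. On multiplicity it states: "a Bonferroni correction will be applied, and primary endpoints tested at the 0.025 level". The 0.025 there is two-sided. The same section puts the operative level at 0.0125 one-sided and ties the claim to the upper limit of a two-sided 97.5% interval for the risk difference being below 20%. A comparison that fails goes on to a superiority test of A against that withdrawal group.

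Sample size {14} agrees: "Due to two primary comparisons, a Bonferroni correction is applied to account for multiple testing", and "Thus, a significance level of 1.25% is used when determining the required sample size". It takes the flare rate in A as 10% and adds that "we assume that the risk of disease flare is equal in all three groups". With a 20% margin and 80% power this gives 43 per group, raised to 150 in total for 15% drop-out.

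Neither section lets the result of one comparison change the level used for the other. The article describes no step-down or recycling of alpha.

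**The concern.** Under single-step Bonferroni both hypotheses are held to one-sided 0.0125 even after one has been rejected. Once that has happened, only one hypothesis is left that could still be rejected in error, and the full one-sided 0.025 can be spent on it. Holm's procedure does this. It needs no ranking of B and C and no assumption about the correlation that arises from the shared control arm. It rejects everything that Bonferroni rejects, and sometimes more.

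What is at stake is the second claim. The trial is small, the Discussion names recruitment as a risk, and the primary objective covers each withdrawal strategy. A second comparison whose upper 95% limit is below 20% but whose upper 97.5% limit is not would be lost under the present rule, although familywise control does not require that.

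**Working it through.** **Inputs.** From Sample size {14}: flare 10% in all arms, margin 0.20, one-sided level 0.0125, power 80%, 43 per group. From Trial design {8}: allocation 1:1:1. Critical values: 2.2414 for one-sided 0.0125 and 1.9600 for one-sided 0.025. Assumption: 43 evaluable patients per arm (50 randomized less 15% is 42.5).

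**1. The plan's own figure.** Unpooled variance term 2 × 0.10 × 0.90 = 0.18.
n = 0.18 × (2.2414 + 0.8416)² / 0.20² = 42.77, rounded up to 43. The stated size reproduces.

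**2. Bonferroni, normal approximation.** SE = √(0.18/43) = 0.0647, and 0.20/0.0647 = 3.091.
- Each comparison: Φ(3.091 − 2.2414) = Φ(0.850) = 80.2%.
- The two statistics share arm A, so their correlation is 0.5 under equal rates. The bivariate normal probability that both exceed 2.2414 is 69.0%.
- At least one: 2 × 80.23% − 69.03% = 91.4%.

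**3. Holm, normal approximation.** The probability that one statistic exceeds 2.2414 and the other exceeds 1.9600 is 73.57%.
- Each comparison: 80.23% + 73.57% − 69.03% = 84.8%.
- Both: 2 × 73.57% − 69.03% = 78.1%.
- At least one: 91.4%, unchanged, because the first step is the same.

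**4. Exact binomial enumeration** (Wald test on raw proportions, 43 per arm, A at 10%; Bonferroni → Holm):

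| True B, C | Power B | Claim of C | Both | At least one |
|---|---|---|---|---|
| 10%, 10% | 78.6% → 85.2% | 78.6% → 85.2% | 63.5% → 76.8% | 93.7%, same |
| 10%, 15% | 78.6% → 81.8% | 45.5% → 55.6% | 38.2% → 51.5% | 85.9%, same |
| 10%, 20% | 78.6% → 79.7% | 19.4% → 26.8% | 16.9% → 25.4% | 81.1%, same |
| 10%, 30% (margin) | 78.6% → 78.6% | 1.6% → 2.8% | 1.5% → 2.8% | 78.7%, same |
| 10%, 60% | 78.6% → 78.6% | 0% → 0% | 0% → 0% | 78.6%, same |

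With all 50 per arm evaluable and 10% everywhere, power for both claims goes from 75.7% to 84.0%.

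**5. Error control.** With B and C both at the margin (10/30/30%), normal theory gives a familywise error of 2.42% under either rule. With C alone at the margin and B at 10%, the error for C goes from 1.25% to 2.45%, within the 2.5% bound. The exact Wald figures are higher (3.1% familywise at 10/30/30% under both rules; 1.6% → 2.8% for C alone) because the Wald test is somewhat liberal at this sample size. A single Wald test at nominal 1.25% already has 1.6%. That belongs to the test used here as a stand-in for the planned model-based interval, and not to the multiplicity rule.

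**The case against.** The strongest reply is that nothing here is wrong. The two sections agree on level, interval and margin; the size of 43 follows from them; and each comparison has the 80% that was planned. All of that stands.

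A reader might infer from 63.5% to 69.0% power for both claims that the trial is underpowered. The documents do not support that. The 80% target was set per comparison, joint power was never a stated goal, and the Discussion says that success of either strategy alone would matter for practice. On that view of success, Holm adds nothing.

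A reader might also infer that Bonferroni has no advantage. It has two. Its simultaneous 97.5% intervals match its decisions exactly, in a plan that words its decision through the interval. It also keeps the stricter level for each withdrawal strategy separately: with one arm at the margin and the other truly non-inferior, Holm nearly doubles the chance of falsely claiming the former (1.25% to 2.45%). A sponsor of a paediatric withdrawal trial may prefer the stricter level.

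Finally, the gain is largest in the planning case. The article's section on benefits and potential harms cites flare rates of 30 to 50% after MTX withdrawal and as high as 60% after TNFi withdrawal. If one arm really performs that badly, the other gains nothing.

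These points limit the weight of the recommendation. They do not remove it: under the plan's own assumption the gain is material, and familywise control is the same.

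**Conclusion.** An inexpensive improvement to a valid rule. Under the plan's assumption of 10% flare in all arms and 43 evaluable per arm, Holm adds about 5 to 7 percentage points of power per comparison and about 9 to 13 points for both claims. The range reflects the normal approximation against exact binomial calculation. The chance of at least one claim does not move.

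The size depends on both withdrawal arms flaring at rates not far from that of group A. With C at 15% it is still about 10 points for C; with C at or beyond 30% it is nil for B. The power figures also rest on an unadjusted Wald test, while the plan uses a risk difference from a logistic model with stratification covariates, so they are approximate. That Holm controls the same familywise error and never rejects less than Bonferroni does not depend on these assumptions.

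**What to change.** In Statistical methods {20a}, with matching wording in Sample size {14}, replace the single-step rule by this one:

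- Test the comparison with the smaller p-value at one-sided 0.0125; claim non-inferiority if its upper 97.5% limit is below 20%.
- If that claim succeeds, test the other comparison at one-sided 0.025; claim non-inferiority if its upper 95% limit is below 20%.
- If the first test fails, claim neither.

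Keep the sample size. Report 97.5% intervals for both comparisons in any case, and state the step-down decision beside them. Reword the step to the superiority test of A so that it refers to a hypothesis left unrejected after the whole procedure.

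Costs: a few sentences in the protocol and the matching text in the SAP; a second decision that may not agree with its 97.5% interval; and an error rate for a single arm at the margin that can rise from 1.25% up to the 2.5% familywise level. The sponsor should accept that last trade-off knowingly or keep Bonferroni.

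The change must precede any comparative look at the data. That looks feasible: Trial status reports 40 participants included, no interim analyses are planned, and the main analyses follow database lock. Because the trial is open-label, the amendment should be dated and should record that no comparison by arm had been made.
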